### Secondary outcomes

Retention in care will be measured by abstracting all scheduled and unscheduled visits from the medical record. We will use these dates to compute retention in care in several ways, following Mugavero et al.’s recommendations about how to define and measure retention in care in the absence of a gold standard [49]. We will first determine “appointment adherence,” the proportion of scheduled visits that are completed during the 0–6 and 6–12 month observation periods. We will also compute the number of “missed visits,” to facilitate comparisons to previous studies, and parameterize this indicator both as a binary and continuous variable for the analysis.Change in food security, as measured by the validated Household Hunger Scale [42] and the Household Dietary Diversity Score [50].Change in BMI, computed as body weight in kilograms (kg) divided by height in meters squared;Weight gain (kg); andViral suppression, measured as the proportion of participants with viral load <400 copies/mL at 6 and 12 months;Self-reported ART adherence, measured with a visual analog scale [51] and defined as the proportion of patients who reported taking all of their prescribed doses in the previous 5 days, averaging across all drugs in the patient's regimen, at 6 and 12 months;Participation in the labor force, including whether the participant is currently working and the number of days the participant was unable to work during the study because of illness or disability.

### Sample size and power

The target sample size for Objective #1 was determined using a non-inferiority design to determine the comparative effect of NAC plus food or cash transfers on ART adherence. Given the emerging evidence demonstrating the benefits of food assistance on ART adherence [13, 14, 16], we determined that the most policy-relevant question was whether NAC plus cash assistance was *at least* as effective as NAC plus food assistance. We estimated that 75 % of participants in the food group would have a MPR ≥95 % based on data from two systematic reviews and a cohort of Tanzanian adults on ART [52–54]. We set a non-inferiority limit (∆) of 10 percentage points, such that that the cash group can have no fewer than 65 % of participants with MPR ≥95 % to be determined non-inferior. With these assumptions, power = 80 % and alpha = 0.025 for a one-sided hypothesis test, 295 participants are required in each of the cash and food transfer arms. Assuming 15 % loss to follow-up, 339 participants are required in each of the food and cash transfer arms. (For comparison, a two-sided test of superiority indicates that that the minimum detectable effect size is 9.3 percentage points with 295 participants per group, assuming 75 % of participants in the food group have a MPR ≥95 %).

To determine whether NAC plus food or cash transfers is better than NAC alone (Objective #2), we require a comparison group of 110 participants to detect at least a 15 percentage point increase in MPR ≥95 % (from 60 % of participants with MPR ≥95 % in the NAC only comparison arm to 75 % in the combined NAC plus food or cash transfer arms), assuming 15 % loss to follow-up and alpha = 0.05. In total, 788 participants are needed for the study.

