**Methods/Design:**

At three HIV care and treatment sites, 788 participants will be randomized into one of three study arms in a 3:3:1 ratio, stratified by site: NAC plus food assistance, NAC plus cash transfer, and NAC only. Eligible participants are: 1) at least 18 years of age; 2) living with HIV infection; 3) initiated ART in the past 90 days; and 4) food insecure, as measured with the Household Hunger Scale. PLHIV who are severely malnourished (body mass index (BMI) < 16 kg/m^2^) will be excluded. Participants randomized to receive food or cash transfers are eligible to receive assistance for up to six months, conditional on attending regularly scheduled visits with their HIV care provider. Participants will be followed for 12 months: the initial 6-month intervention period and then for another 6 months post-intervention. The primary outcome is ART adherence measured with the medication possession ratio. Secondary outcomes include 1) retention in care; 2) nutritional indicators including changes in food security, BMI, and weight gain; 3) viral suppression and self-reported ART adherence; and 4) participation in the labor force.

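### The 339 per transfer arm adds 15% to 295 instead of dividing by 0.85, so at the planned 15% loss Objective 1 has about 79% power rather than 80% (a minor slip)

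*Protocol article*

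**What the plan says.** The Sample size and power section of the protocol article sets out the Objective 1 calculation in this order:

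- Response rate: "We estimated that 75 % of participants in the food group would have a MPR ≥95"%.
- Margin: "We set a non-inferiority limit (∆) of 10 percentage points".
- Error rates: "power = 80 % and alpha = 0.025 for a one-sided hypothesis test".
- Evaluable number: "295 participants are required in each of the cash and food transfer arms".
- Number after allowing for 15% loss: "339 participants are required in each of the food and cash transfer arms".

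The next paragraph gives 110 for the counseling-only (NAC) arm, also described as allowing for 15% loss, and concludes: "In total, 788 participants are needed for the study". The total is 339 + 339 + 110 = 788. The abstract repeats it: "788 participants will be randomized into one of three study arms". The article does not state the formula used to allow for loss.

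**The concern.** The 295 and the 339 cannot both be right at 15% loss. If 295 evaluable participants are needed and 15% of those enrolled are lost, the enrolled number must satisfy 0.85 × N ≥ 295. Adding 15% to the evaluable number does not achieve this, because the loss applies to the larger, enrolled number.

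Objective 1 is a primary objective and its calculation has almost no slack: 294.3 is rounded up to 295 at 80% power. Any shortfall in the allowance for loss therefore takes power below the stated figure. The affected number also feeds the headline sample size in the abstract.

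**Working it through.** **Inputs** (all from Sample size and power): proportion with MPR ≥95% of 0.75 in the food arm, taken as equal in the cash arm; margin 0.10; one-sided alpha 0.025 (z = 1.96); power 80% (z = 0.8416); loss 15%.

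**1. Reproduce the evaluable number.**

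n = (1.96 + 0.8416)² × 2 × 0.75 × 0.25 / 0.10² = 294.3, rounded up to 295 per arm. This matches the article.

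**2. Find where 339 comes from.**

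- Multiplying: 295 × 1.15 = 339.25, which rounds to 339. This matches.
- Dividing: 295 / 0.85 = 347.06, rounded up to 348. This does not match.

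**3. See what 339 delivers.**

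- Evaluable at 15% loss: 339 × 0.85 = 288.15, so 288 per arm, 7 fewer than 295.
- Largest loss that still leaves 295: 1 − 295/339 = 12.98%, about 13%.
- Shortfall in enrolment: 348 − 339 = 9 per arm, or 9/348 = 2.6%.

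**4. Power at each evaluable number.** Power = Φ(0.10 / √(2 × 0.75 × 0.25 / n) − 1.96).

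| Evaluable per arm | Standard error | Power |
|---|---|---|
| 295 | √(0.375/295) = 0.03565 | Φ(0.845) = 80.1% |
| 288 | √(0.375/288) = 0.03608 | Φ(0.811) = 79.1% |

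**5. Effect on the total.**

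- Correcting only the two transfer arms: 2 × 348 + 110 = 806, which is 18 more than 788.
- Reaching 348 per transfer arm under 3:3:1 randomization: the NAC arm becomes 348/3 = 116, and 2 × 348 + 116 = 812, which is 24 more than 788.

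**6. Does the 110 carry the same slip?** The article gives neither the power nor the formula behind it, so this can only be inferred. A continuity-corrected comparison of 60% with 75%, allocation 1:6, two-sided alpha 0.05 and an assumed 80% power gives 93. Then 93/0.85 = 109.4, rounded up to 110, whereas 93 × 1.15 = 106.95, that is 107. On that reading the 110 was inflated correctly.

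**7. Expected split of 788 under 3:3:1.** 788 × 3/7 = 337.7 and 788/7 = 112.6, so about 338:338:113 against the stated 339:339:110.

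**The case against.** The strongest reply is that the slip changes nothing of substance. A loss of 0.9 of a percentage point of power is small beside the uncertainty in the planning values of 75% adherence and 15% loss. Non-inferiority will be judged on the observed confidence interval, not on planned power. This stands, and it is why the point is minor.

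A second reply is that fewer than 15% may drop out of the primary analysis. Under Primary outcome and Data collection, MPR comes from pharmacy records, and the modified intent-to-treat set in the Analysis plan needs only one post-enrollment visit, so someone who misses the 6-month interview may still be evaluable. That is plausible, but the article does not quantify it. It bears on the loss that will actually occur, not on whether 339 follows from 295 at the 15% that the plan assumes.

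Four stronger readings are tempting, and the document does not support them:

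- *The trial is materially underpowered.* By the plan's own inputs it has about 79.1% power at 15% loss, and it keeps 80% if loss stays at or below about 13%.
- *The whole 788 was inflated wrongly.* Only the two 339s show the slip. The 110 has no stated formula and is consistent with correct division.
- *The 784 enrolled by June 2015 makes it worse.* Study status gives that count without arm totals and does not say that enrolment had closed, so it cannot be used as the final sample size.
- *The 339:339:110 split is an error because randomization is 3:3:1.* The first is a set of requirements per arm and the second a practical ratio. The difference is about one participant fewer in each transfer arm and about three more in the NAC arm, with negligible effect on power.

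**Conclusion.** The point holds as a minor arithmetic error. The 339 per transfer arm is 295 × 1.15, and the plan's own 15% loss requires 348. As written, 339 leaves 288 evaluable per arm and Objective 1 power of about 79.1% against the stated 80%. Through the two 339s, the total of 788 is 18 below the corrected 806 (NAC kept at 110), or 24 below 812 under 3:3:1.

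That 339 is insufficient at 15% loss needs no assumption beyond the article's 295. The power figures rest on equal true proportions of 75% in both arms, the unpooled normal approximation that reproduces 295, loss of exactly 15% in each arm, and the one-sided 0.025 level stated in the sample size section. That the 110 was inflated correctly is an inference and the verdict does not depend on it.

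**What to change.** Do not enrol more participants on this account. Correct the sample size text, for example:

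> *With 339 enrolled per transfer arm, 295 are evaluable (80% power) if loss is at most about 13%; at 15% loss, 288 per arm are evaluable and power for Objective 1 is about 79%.*

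If the authors prefer to state the requirement at 15% loss, it is 348 per transfer arm, with a total of 806 (NAC arm at 110) or 812 (3:3:1 kept), next to the 788 planned. Optionally, add that 788 randomized 3:3:1 is expected to give about 338:338:113.

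The cost is a text correction and a slightly less favourable power statement. Design, margin and analysis are unaffected.

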### Analysis plan

We will first conduct a modified intent-to-treat analysis including participants with at least one post-enrollment visit. We will express the relationship between treatment arm (NAC, NAC plus food assistance, and NAC plus cash transfer) and MPR ≥95 % as risk differences with 95 % confidence intervals (CI). CIs will be adjusted for multiple comparisons between the three treatment groups using Bonferroni’s adjustment and the *pwcompare* compare command in Stata 14 (College Station, Texas).

To assess Objective 1, we will compare the proportion of individuals with MPR ≥95 % among those receiving NAC plus food to those receiving NAC plus cash transfers at 6 months. Only Objective 1 will be assessed in terms of non-inferiority; all other comparisons will be tests for superiority. The proportion of participants with MPR ≥95 % in both groups and the associated two-sided 95 % CI for the difference will be estimated. Non-inferiority of NAC plus cash transfers will be defined as the lower 95 % CI of the between-group difference in the primary outcome lying above a threshold of −10 % [55, 56]. If non-inferiority is evident, we will then assess whether NAC plus cash transfers is superior to NAC plus food transfers using a Wald test with alpha = 0.05.

To assess Objective 2, if the NAC plus food and cash transfer groups are not statistically different from each other based on examination of 95 % confidence intervals, we will pool the groups together and create a binary explanatory variable indicating NAC alone or NAC plus cash or food. We will then examine the effect of receiving NAC plus food or cash assistance on ART adherence compared to NAC alone.

We will potentially conduct two secondary analyses. First, if the randomization scheme produces imbalanced baseline characteristics among study participants in each of the three groups, these covariates will be included in regression models to generate adjusted risk differences and 95 % CIs. In addition, we will conduct a per protocol analysis using data from participants who received at least a minimum exposure to the interventions and for whom MPR was available at 6 months. Thus, we will construct a regression model with the 3-level treatment group and restrict the intervention groups to individuals who received ≥1 food basket or cash transfer during the 6-month intervention period.

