## Methods

### Study setting and design

In Tanzania, 1,500,000 people are living with HIV infection and 399,886 are on ART [36]. The Global Hunger Index is 17.3, indicating serious levels of hunger [37]. The study is conducted in Shinyanga Region, a resource-poor region in the northwest “Lake Zone” of Tanzania where approximately 17 % of households have poor or borderline food consumption and HIV prevalence is 7.4 %, making this an ideal setting to examine how food and cash assistance may influence adherence to ART [38, 39].

We designed a 3-arm parallel group randomized trial to examine the effectiveness of short-term food and cash assistance added to the standard of care HIV services, including nutrition assessment and counseling (NAC). We include a standard-of-care comparison group that does not receive food or cash transfers. Participants will be recruited from 3 facilities,^1^ randomized to one of three study arms, and followed for 12 months: during the 6 month intervention period and then for another 6 months post-intervention. All sites participating in the study are currently trained in and implementing the President’s Emergency Plan for AIDS Relief (PEPFAR) Nutrition Assessment, Counseling, and Support (NACS) program [40].

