### Interventions

Participants are randomized to one of three study arms: NAC alone (comparison condition), NAC plus food assistance, and NAC plus cash transfers.NAC alone (comparison condition): Participants in the comparison arm receive the standard HIV primary care services available at HIV care and treatment clinics in Tanzania, including NAC.NAC plus food assistance: Participants in the NAC plus food assistance arm receive the standard of care services plus the opportunity to receive a monthly food basket for up to 6 consecutive months, conditional on attending their scheduled visits with their HIV care provider, which are typically monthly. The food basket consists of locally procured whole maize meal (12 kg), groundnuts (3 kg), and beans (3 kg). The composition of the food basket was determined with the input of experts in academic, government, and donor organizations and was selected to be applicable to other settings, not cost-prohibitive, and use foods available in the local markets. The food basket is intended to *supplement* the household’s food supply and is not intended to provide all of the required nutritional needs for all household members. Participants receive a targeted counseling message that “*this food is to help you stay healthy as you continue your HIV treatment, and you should use it to help you take your HIV medicine as your doctor has recommended.”* (A similar message is given to cash transfer recipients.) Food baskets (and cash transfers, described below) are distributed on the same two days per month for consistency.NAC plus cash transfer: Participants in the NAC plus cash transfer arm receive all of the standard of care services plus the opportunity to receive a monthly cash transfer for up to 6 consecutive months, conditional on attending scheduled visits with their HIV care provider. The cash transfer is 22,500 Tanzanian Shillings (approximately $11 USD) exclusive of transaction fees and is equivalently valued to the food basket. This value was selected to prevent undue coercion to study participants and to be consistent with the Tanzania Social Action Fund (TASAF), a government-run anti-poverty program which targets “orphans, disabled, elderly, widows/widowers, and those infected or affected by HIV/AIDS*,”* among other vulnerable groups [43]. TASAF provides $6-18 monthly to households depending on the presence and number of vulnerable children and elderly members. The transfer for this study, at ~ $11, is within this range, ensuring that the amount is policy-relevant. Cash is transferred to participants via a mobile money service (i.e., M-PESA) and transaction fees are paid by the research study. In the rare case that a participant does not have a cell phone, we will provide cash directly.

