
#### Conditionality

Participants in the food or cash assistance arms of the study are eligible to receive transfers for up to the first 6 consecutive months of the study, conditional on attending their scheduled visit with their HIV care provider. Trained research assistants consult the medical record to verify visit attendance. (In rare instances when visits are scheduled 60 or 90 days apart by the provider, participants receive the total value of 2 or 3 monthly transfers, respectively, if they attend the scheduled visit). After a detailed review of scheduling patterns, we developed a decision rule for eligible visits: transfers can only be made once every 26 days (to ensure that no one receives a transfer more than once every 4 weeks), and the actual visit must occur within a 4 day window (+/− 4 days) from the scheduled visit to encourage adherence to the physician’s recommended monitoring plan.

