### Randomization

Participants are randomized into the food, cash, and comparison arms in a 3:3:1 ratio, stratified by site, using random permuted block sizes of 7, 14, and 21. Randomization procedures were conducted at the University of California, Berkeley and the procedures and group assignments were inaccessible to the local research team. Randomization assignments were listed in opaque sealed envelopes that were sequentially numbered. After participants provided written informed consent, trained research staff at study clinics selected the next envelope in numeric order and broke the seal to reveal the randomization assignment. Due to logistical considerations, participants and investigators were not blinded to intervention assignments.

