### Data collection

A comprehensive in-person interview about individual and household characteristics, food security, ART adherence, and health service utilization will be conducted at baseline, 6 and 12 months along with quantification of plasma viral load. Visit attendance, CD4 count, pharmacy pick-up data, and other clinical and prognostic markers will be abstracted from medical and pharmacy records at 0, 6, and 12 months.

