### Primary outcome

The primary outcome is ART adherence at 6 months, measured with the medication possession ratio (MPR), the proportion of time an individual is in possession of >1 ART dose or prescription for ART [44]. MPR is computed from pharmacy dispensing records as the number of days ARVs are prescribed or dispensed divided by the number of days in the interval, and has been shown to be associated with short-term virologic outcomes [44–47]. We will determine the proportion of patients with MPR ≥95 % (the 95 % cutpoint is based on prior studies [48]) during the 0–6 month interval (primary outcome).

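### The primary analysis set requires a post-randomisation visit that only the transfer arms are paid to attend, which biases Objective 2 and leaves Objective 1 without the protection of randomisation

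*Protocol article*

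**What the plan says.** The Analysis plan section sets the leading analysis: "We will first conduct a modified intent-to-treat analysis including participants with at least one post-enrollment visit". The only other set it describes is a per-protocol set, which requires at least one basket or transfer in the intervention arms and sets no matching rule for NAC alone. No analysis of everyone randomised is described.

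Under Interventions, the food basket is "conditional on attending their scheduled visits with their HIV care provider", and cash carries the same condition. The Conditionality section repeats this for both arms: "conditional on attending their scheduled visit with their HIV care provider". The third arm has no such reward: "We include a standard-of-care comparison group that does not receive food or cash transfers" (Study setting and design). The trial is open label: "participants and investigators were not blinded to intervention assignments" (Randomization).

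The primary outcome does not need a study visit. Under Primary outcome, "MPR is computed from pharmacy dispensing records as the number of days ARVs are prescribed or dispensed", divided by the days in the interval, with success defined as MPR of at least 95% over months 0–6. Under Data collection, "pharmacy pick-up data, and other clinical and prognostic markers will be abstracted from medical and pharmacy records at 0, 6, and 12 months".

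**The concern.** Membership of the analysis set depends on something that happens after randomisation and that treatment is designed to change. Attendance is rewarded in two arms and not in the third, and retention in care is itself a secondary outcome. Those the rule removes are almost all failures on the primary outcome, so it conditions on something close to the outcome itself.

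For Objective 2 (transfers against NAC alone), bringing people back to the clinic is part of the effect. Dropping those who never come back removes part of that effect from view. For Objective 1 (cash against food), the comparison no longer rests on randomisation alone. It also needs the two arms to lose similar shares.

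**Working it through.** **Inputs from the article (Sample size and power).** Rates of MPR ≥95%: 75% in the transfer arms, 60% in NAC. Arm sizes: 339 + 339 = 678 transfers and 110 NAC. Margin 10 points, one-sided alpha 0.025, 80% power, 15% loss to follow-up.

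**Inputs assumed.** The share q with no post-enrolment visit is not given. The values below lie between 0% and the stated 15% total loss. I take 75% and 60% as the rates among all randomised, and treat everyone excluded as a failure.

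**Step 1: the plan's own figure.** (1.960 + 0.842)² × 2 × 0.75 × 0.25 / 0.10² = 294.3, so 295 per arm. This matches the article.

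**Step 2: are those excluded failures?** Visits are typically monthly; the longest spacing mentioned is "In rare instances when visits are scheduled 60 or 90 days apart by the provider". If supply follows the visit interval, a person who never returns has at most about 90/180 = 50% of the interval covered, well below 95%.

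**Step 3: Objective 2.** With p the rate among all randomised, the analysed rate is p / (1 − q). The analysed numbers are 678(1 − q) and 110(1 − q). Power is Φ(difference / SE − 1.96), with the unpooled Wald SE and no multiplicity adjustment.

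| Excluded: transfers / NAC | Analysed rates | Difference (points) | Power |
|---|---|---|---|
| 0% / 0% | 75.0% v 60.0% | 15.0 | 86% |
| 1% / 2% | 75.8% v 61.2% | 14.5 | 83% |
| 2% / 5% | 76.5% v 63.2% | 13.4 | 76% |
| 5% / 10% | 78.9% v 66.7% | 12.3 | 69% |
| 5% / 12% | 78.9% v 68.2% | 10.8 | 58% |
| 5% / 5% | 78.9% v 63.2% | 15.8 | 89% |

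Example, 5% / 10%: 0.75/0.95 − 0.60/0.90 = 0.789 − 0.667 = 0.123. A pooled-variance power formula gives somewhat higher values (89% with no exclusion, 75% at 5% / 10%), with the same pattern. NAC is small, so few people matter: 10% of 110 is 11 participants.

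**Step 4: Objective 1 at the margin.** Take true rates of 65% (cash) and 75% (food), with 339 per arm. The chance of wrongly declaring non-inferiority is Φ((difference + 0.10) / SE − 1.96).

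| Excluded: cash / food | Analysed difference (points) | One-sided type I error |
|---|---|---|
| 0% / 0% | −10.0 | 2.5% |
| 5% / 5% | −10.5 | 1.7% |
| 5% / 2% | −8.1 | 7.8% |
| 2% / 5% | −12.6 | 0.3% |

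Example, 5% / 2%: 0.65/0.95 − 0.75/0.98 = 0.684 − 0.765 = −0.081; SE 0.0348; Φ(0.0189/0.0348 − 1.96) = 0.078. If the true rates are equal and exclusion is equal, the analysed difference stays at 0.

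**The case against.** **A reader might infer that both primary comparisons are biased.** The article does not support that for Objective 1. Food and cash share the attendance condition, the visit-window rule, an equivalent value and the distribution days. Nothing in it predicts that one arm loses more never-returners than the other. Equal exclusion leaves a true null at 0 and makes the test slightly conservative at the margin. Only an unevidenced gap would do harm. This objection stands.

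**A reader might also infer that the Objective 2 effect is certainly and substantially diluted.** That is not supported either. Participants are already on ART with typically monthly visits, and a single visit may be enough for inclusion. At 1% against 2% the loss is half a point, and equal exclusion pushes the other way. This stands: both size and direction depend on rates the article does not give.

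**The power baseline.** The plan allows for 15% loss. With that loss and rates held at 75% and 60%, the same Wald formula gives about 80%, not 86%. The power column therefore compares with analysing all 788, not with the planned level.

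**The planning rates may already refer to evaluable participants.** In that case 15 points is the effect in the analysed set. The distortion remains: at 5% / 10% exclusion the all-randomised difference would be 0.75 × 0.95 − 0.60 × 0.90 = 0.7125 − 0.540 = 17.25 points, and the visit-based analysis would report 15.

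**The word visit is undefined.** It could mean a clinic visit or a study interview, and the link to payment is direct only for the former. This stands as an assumption.

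**No dispensing on record is not proof of no possession.** People die or move to another clinic, and the per-protocol wording shows that the authors expect MPR to be unavailable for some. This is fair, and the fix must handle it.

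**The rule is disclosed and is the same in every arm.** True, but an identical rule does not give comparable exclusions when only some arms are paid to satisfy it.

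**Conclusion.** The concern holds for Objective 2. The leading analysis selects on a post-randomisation behaviour that is rewarded in two arms and not in the third, and those it removes are almost all failures. If payment brings people back, the effect is understated; if exclusion is equal, it is slightly overstated. Under the assumed shares, the analysed difference runs from 10.8 to 15.8 points against a true 15.0, and Wald power from 58% to 89% against 86%. If nearly everyone returns once, the distortion is negligible.

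Objective 1 is not shown to be biased. It is left unprotected, because its error rate depends on the food and cash arms losing similar shares; an assumed 5% cash against 2% food takes it from 2.5% to about 7.8%.

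The conclusion rests on three assumptions: that visit means an HIV clinic visit, that never-returners have MPR below 95%, and that the exclusion shares are of the order shown. Because the outcome comes from pharmacy records, the plan need not carry this risk.

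**What to change.** - Make the primary analysis set all randomised participants, as assigned. Compute months 0–6 MPR from pharmacy records, counting no dispensing after enrolment as no possession beyond stock on hand.
- Keep the visit-based set as a sensitivity analysis, define visit, and report the number excluded by arm.
- Add a sensitivity analysis that handles documented deaths and transfers-out separately.

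The cost is a change of wording and pharmacy abstraction for those who never returned. The required sample size does not change, and with 784 participants enrolled by June 2015 (Study status) no design change is needed. There is a small downside: people who moved to another clinic without documentation may hold ARVs the site cannot see, and would count as non-adherent.

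### The analysis plan Bonferroni-adjusts the intervals among all three arms without exempting cash versus food, although Objective 1 is sized and decided at an unadjusted level; if the adjusted interval decides, non-inferiority power is about 66%, not 80%

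*Protocol article*

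**What the plan says.** The first paragraph of the Analysis plan expresses the relation between the three arms and MPR ≥95% as risk differences with 95% confidence intervals. It then adds: "CIs will be adjusted for multiple comparisons between the three treatment groups using Bonferroni". No pair of arms is excluded.

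The second paragraph gives the rule for Objective 1. It calls for a two-sided 95% interval for the cash–food difference and continues: "Non-inferiority of NAC plus cash transfers will be defined as the lower" limit of that interval lying above −10%. If non-inferiority is shown, superiority of cash over food is tested by a Wald test at alpha 0.05. Neither step mentions adjustment.

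Sample size and power sets the design values for the same contrast: "We estimated that 75 % of participants in the food group would have a MPR ≥95"%, "We set a non-inferiority limit (∆) of 10 percentage points", and "power = 80 % and alpha = 0.025 for a one-sided hypothesis test". From these it concludes that "295 participants are required in each of the cash and food transfer arms". No allowance for multiple comparisons appears there. Objective 2, the pooled transfer arms against NAC alone, is sized at alpha 0.05.

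**The concern.** Three arms make three pairwise contrasts, and cash versus food is one of them. Read literally, the Bonferroni sentence turns its interval into a 98.33% interval. The Objective 1 paragraph and the sample size point instead to an ordinary 95% interval. Two intervals are therefore available for one primary decision.

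The label does not settle which is meant. The first paragraph also calls its intervals 95% intervals before saying that they will be adjusted, so the same label in the Objective 1 rule could refer to either.

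Two things are at stake. If the adjusted interval decides, the trial has well below its stated power for its first primary objective. And if the choice is still open when data are seen, in a trial where investigators are not blinded (Randomization), the non-inferiority verdict could depend on which interval is reported. The Discussion ties that verdict to policy on cash against food support.

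**Working it through.** **Inputs**
- From Sample size and power: 75% with MPR ≥95% in the food arm; margin 10 points; one-sided alpha 0.025; power 80%; 295 evaluable and 339 enrolled per arm ("Assuming 15 % loss to follow-up, 339 participants are required in each of the food and cash transfer arms").
- Assumed: a true rate of 75% in the cash arm as well, which is what the stated size implies; unpooled variance; three pairwise comparisons in the Bonferroni adjustment.

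**Step 1: reproduce the plan's size**

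n per arm = (z₀.₉₇₅ + z₀.₈₀)² × 2p(1−p) / Δ² = (1.960 + 0.842)² × 2 × 0.75 × 0.25 / 0.10² = 294.3, which rounds up to 295. This matches the article, so the size rests on an unadjusted 95% interval.

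**Step 2: adjusted level**

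Bonferroni over three comparisons gives intervals at 1 − 0.05/3 = 98.33%. The one-sided level is 0.05/6 = 0.00833 and z = 2.394.

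**Step 3: power under each interval**

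Power = Φ(Δ/SE − z), with SE = √(2 × 0.75 × 0.25 / n).

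At n = 295, SE = √(0.375/295) = 0.03565 and Δ/SE = 2.805.
- Unadjusted: Φ(2.805 − 1.960) = Φ(0.845) = 80.1%.
- Bonferroni: Φ(2.805 − 2.394) = Φ(0.411) = 65.9%.

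| Evaluable per arm | Unadjusted 95% interval | Bonferroni 98.33% interval |
|---|---|---|
| 288 (339 × 0.85) | 79.1% | 64.7% |
| 295 (stated) | 80.1% | 65.9% |
| 339 (no loss) | 85.2% | 73.0% |

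**Step 4: what the difference means for the verdict**

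At 295 per arm the half-widths are 1.960 × 3.565 = 6.99 points and 2.394 × 3.565 = 8.54 points. Non-inferiority then requires an observed cash deficit below 10 − 6.99 = 3.0 points with the unadjusted interval, or below 10 − 8.54 = 1.5 points with the adjusted one. An observed deficit between about 1.5 and 3.0 points passes one rule and fails the other. With truly equal arms this happens in about 80.1 − 65.9 = 14.2% of trials.

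**Step 5: size that the adjusted interval would need**

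(2.394 + 0.842)² × 0.375 / 0.01 = 392.7, so 393 evaluable per arm. Study status reports 784 of the planned 788 already enrolled, so this shows the scale of the gap and is not a practical remedy.

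**The case against.** The strongest reply is that the specific rule governs the general one. The Objective 1 paragraph has its own interval, threshold and superiority level, and the sizing alpha agrees with them. On that reading the decision uses the unadjusted interval and the 80% power stands. This carries weight: it is the better-supported reading and the one to confirm. What remains is that the article never states it, while the Bonferroni sentence on its face includes the cash–food contrast.

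A second reply is that the unseen statistical analysis plan would settle the matter. It may do so, but the issue here is two statements that pull apart in the published text, not an omitted detail.

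A third is that the adjusted rule is the stricter one, so it cannot raise the risk of a false non-inferiority claim. That is correct; its cost is power alone.

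Two stronger inferences should be resisted. A reader might conclude that the trial simply is underpowered for non-inferiority. The documents do not support that, because the shortfall exists only if the adjusted interval decides. A reader might also carry the power loss over to Objective 2. The Bonferroni sentence concerns comparisons among the three groups, whereas the pooled Objective 2 analysis is one contrast on a binary variable. Nothing in the text places that contrast under the adjustment.

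**Conclusion.** The point holds as a conflict over which interval decides Objective 1. With the Bonferroni interval, power is 65.9% at the stated 295 evaluable per arm and 73.0% if all 339 are evaluable, against a stated 80%. With the unadjusted interval, the stated 80% is right and only the wording is at fault. The figures assume equal true rates of 75%, the 10-point margin, unpooled variance and three pairwise comparisons. The modified intent-to-treat set could exceed 295 per arm, but even with no loss the adjusted interval falls short of 80%. The sizing and the Objective 1 rule both favour the unadjusted reading. Because the primary verdict can turn on the choice, it should be put in writing before the primary analysis.

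**What to change.** Amend the Analysis plan to state three things:

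1. Objective 1 is decided on the unadjusted two-sided 95% interval (one-sided 0.025), as sized. The superiority test at 0.05 that follows needs no further adjustment, because it is a closed sequence on the same contrast: a lower limit above zero is already above −10 points.
2. The Bonferroni adjustment applies to the other pairwise comparisons. These include food versus NAC alone and cash versus NAC alone if the two transfer arms are not pooled, since pooling in the plan is conditional on the arms not differing.
3. The adjustment does not apply to the single pooled Objective 2 contrast, which was sized at alpha 0.05.

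The cost is a few sentences. Sample size, data collection and the non-inferiority margin are unchanged.
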